### Intervention

#### CARE-CITE-Gait Intervention

The CARE-CITE-Gait intervention will occur over 4 weeks in the dyad’s home with CP reviewing the CARE-CITE-Gait modules via a web platform (See Table 2). The research interventionist will conduct two-hour, in-home visits at weeks 1 and 4 to develop collaborative goal-setting, and teleconference (phone) check-ins during weeks 2 and 3. At the beginning of each in-home visit, the research interventionist will incorporate clinical assessments of gait function and mobility (5 Times Sit-to-Stand, Timed Up and Go, 10-meter walk; see Table 1 for study schedule and Table 3 for outcome measure description) that mirror lab-based measurements to guide the development of a personalized therapeutic exercise program within the context of each dyad’s unique home environment. In addition to guiding the intervention clinical decision-making for SS and CP goal setting, these additional measurements will provide preliminary data for future validation of non-blinded versus more rigorous blinded in-lab assessments in future study designs.

1) Week 1 Visit - Orientation (2 hours): The research interventionist will meet with CP and SS to review collaborative goals setting, evaluate lower extremity movement, balance, and gait limitations, and identify functional activity preferences and goals. Together, the CP, SS, and interventionist will initiate the development of a progressive therapeutic exercise plan for home-based functional task practice targeting gait and mobility, determine activities or sub-tasks for each goal, develop measurable milestones to accomplish during the treatment period, and create a framework to improve joint responsibilities for self-management skills.

2) CP completes 6 online CARE-CITE modules (15-30-minute sessions each): At the end of the second baseline evaluation, the project coordinator will instruct the CP in the procedures for accessing and viewing the online modules, provide the CARE-CITE-Gait website access password, and guide the CP to review as many modules as possible prior to the first home visit. During Visit 1, the interventionist will review any accessibility issues with the CP and encourage the completion of all 6 modules during the remaining study period. Modules will include demonstration videos and instructive content covering the following areas: principles of functional task practice (i.e., standing and mobility-based activities of daily living such as meal preparation, grooming, household ambulation, or leisure/vocational activities), the adaptation of tasks, and the importance of progressing task challenge and dosage to drive neuroplasticity (i.e., increasing numbers of practice repetitions, walking distance, or balance exercise duration). Examples are provided to address potential SS frustration and improve adherence. Underpinning the content is the concept of autonomy support, with examples of fostering empathy (e.g., the CP joining the SS in walking program), problem-solving (guidance for adaptation of functional activities at home to increase success or challenge), instruction in the use of non-controlling language with role-playing situations and the importance of creating choice in activities. For example, in one vignette to demonstrate problem-solving, a CP interacts with the SS during a standing meal preparation activity and uses non-controlling language to offer choice for task modifications for maintaining balance while reaching for kitchen utensils. The SS becomes frustrated with the challenging task, and the CP demonstrates options for dialogue that foster collaborative problem-solving.

3) Week 2 and 3 telephone check-ins: During weeks 2 and 3 in the 4-week intervention, the research interventionist will complete a structured 10-minute phone call with CP to answer questions, ask the CPs to identify two challenging areas during SS practice activities, and CP opportunities to use autonomy-supportive strategies.

4) Week 4 Home visit (2 hours): At the end of week 4, the same research interventionist will visit the home to review progress with milestones and advancement of activity goals.

#### Standardization

To increase rigor and minimize bias, evaluators will be blinded to study hypotheses/intervention and will be trained in study procedures (e.g., 6-minute walk test) by the PI (SB) and Co-I (TK) with regular assessments of competence every 1.5 months. All efforts will be made to pair the same evaluator with the same dyad for all evaluations to reduce variability. The PI and Co-I will train the research interventionist in delivering the intervention. The PI will provide supervision for the initial in-home visits and phone calls (first 5 dyads) and review the remaining dyad interventions through regular check-ins after each intervention is completed (via email or phone communication). To facilitate protocol adherence, data collection forms for both evaluations and the intervention will be standardized. The laboratory adheres to Good Laboratory Practice[31] principles for clinical research. Working with University Diversity Equity and Inclusion office resources, all study personnel will receive ongoing cultural diversity training throughout the study that will foster education, self-awareness, communication, and community engagement.

### Outcomes

The primary objective of Phase I is to evaluate the content validity and user satisfaction of CARE-CITE-Gait. The primary objective of phase II is to determine the feasibility of CARE-CITE-Gait and our planned study procedures. The secondary objective is to determine the preliminary effects of the CARE-CITE-Gait intervention on both SS and CPs. Measures of CP psychosocial outcomes and SS physical function, gait, and hrQOL will be administered at the rehabilitation hospital stroke research laboratory (in separate rooms) before and after the 4-week intervention (immediately and at 1-month follow-up). See the brief descriptions below and Table 4. Between baselines and after post- and follow-up assessments, SS home and community stepping activity (accelerometry) will be assessed. A select set of measures of SS functional mobility and gait function will also be assessed at intervention home visits to determine the feasibility of assessing outcome measures.

#### Content validity and user satisfaction of CARE-CITE-Gait

In Phase I, we will draw on similar procedures from our previous work [21] evaluating the content validity and user satisfaction of the upper extremity CARE-CITE intervention. To assess CARE-CITE-Gait content validity, content experts (experienced stroke rehabilitation researchers and clinicians) will complete investigator-designed content forms which score the degree to which the content in each module addresses the problem relevance within each content domain. Forms are adapted based on work by Bakas and colleagues. [32] Rehabilitation experts will review the modules for accuracy of content, feasibility, acceptability, problem relevance, and ease of use, using a 5-point Likert response scale (ranging from 1 = strongly disagree to 5 = strongly agree). Nine open-ended reflection questions will gather qualitative feedback regarding most and least helpful modules, areas of concern, areas for improvement, and applicability to clinical practice. Scores will be averaged across each domain for the experts. Experts will review the reflection questions at the end of each module and provide general comments and suggestions for improving content.

To assess CARE-CITE-Gait user satisfaction (usability, acceptability, and overall satisfaction), we will use adapted questions (based on work by Bakas and colleagues [32]) which will be completed by the CP immediately after reviewing of each of the six modules. Satisfaction will be defined as: 1) usefulness of overall content, 2) usefulness of written text, 3) usefulness of videos, 4) ease of use, and 5) acceptability. Each area will be rated using a 5-point Likert type response scale ranging from *1 = strongly disagree* to *5 = strongly agree* and average scores calculated for each subscale as well as a total score. Additionally, time (minutes) to review modules will be recorded by the CP and one open-ended question will be used for general comments or improvement suggestions.

#### Feasibility

To assess the feasibility of the study protocol in Phase II, we will assess participant recruitment and retention, SS and CP adherence to the intervention, and safety (occurrence and type of SS adverse events). The definition and criteria for success are noted in Table 3. We will record the reasons for ineligibility or declining to participate and reasons for study withdrawal after enrollment (obtaining signed consent) in the Consolidated Standards of Reporting Trials (CONSORT) flowchart.

Additional measures of feasibility will include the assessment of CP’s perceptions of CARE-CITE-Gait usability and satisfaction during the one-month intervention period (similar to procedures in Phase I, above). At the end of the one-month follow-up evaluation, CPs will complete the standardized Post Study System Usability Cuestionnaire [33] and a three-section CP Exit Interview questionnaire. Based on post-study participation interviews in similar stroke research [34], this investigator-developed Exit Interview questionnaire was reviewed by experts in caregiving and stroke for content validity. The first section addresses CP confidence in care with sample questions such as: “How confident are you that you can encourage your loved-one when she/he is frustrated with a task?” (15-items, with response scale of 0-100 (0-very uncertain, to 100-very certain)). The second section evaluates the value of participation in the study with questions such as: “Given the time commitment and effort for you to take part in the education project and its effect on your ability to help your loved one, how worthwhile has the participation in the education project been to you personally?” (5 items with a response scale of 1-7 (i.e., 1-not worthwhile to 7-very worthwhile) and two open-ended questions). The third section assesses aspects of helpfulness for the intervention such as: “Given your experience with the education project, how helpful do you feel each of the following aspects (being able to view intervention from your home; homework activities between sessions, the format of using CARE-CITE-Gait website) was for achieving results in your particular case?” with a response scale of 1-7 (i.e., 1-not helpful at all, to 7- very helpful). Two additional open-ended questions ask about helpful areas of the intervention and areas for improvement.

#### Outcomes for Carepartner and Stroke Survivor

Each standardized tool used in Phase II has been tested in the stroke population previously. Table 4 lists CP and SS outcome measures, descriptions, and established reliability and validity. Psychosocial outcomes measured for the CP include family conflict about stroke recovery, strain, autonomy support, and quality of life changes. Outcomes measured for the SS include functional mobility, gait speed, stepping activity, and hrQOL.

#### Additional Assessments

Medical records (for SS) and information questionnaires (SS and CP) will be used to document data about participant characteristics. Information collected for the dyad (both SS and CP) includes demographics (age, gender), marital status, education level, income, work status, any changes in work since stroke, co-morbidities, COVID (past history of testing positive and vaccinations), and current medications. To evaluate adequate participant diversity in recruitment, we will document participants’ self-identified race and ethnicity. From the dyad primary living location zip code, we will determine the Area Deprivation Index (ADI)[35], which characterizes the relative disadvantage of an individual or social network using several US Census indicators of employment, housing, poverty, and education [36]. This collection of data will help guide our recruitment so that we have a diverse and inclusive participant sample based on socioeconomic status as well as race and ethnicity. Specific information gathered for the SS includes the type of stroke, time post-stroke, usual and customary care rehabilitation therapy received (dosage, duration, and frequency), and use of assistive device and/or lower extremity orthotic for mobility. For CP, information collected includes relationship to SS and status of serving as caregiver for other members of family besides SS.

#### Step activity data

To gain information about real-world stepping activity at home and in the community, the SS will be provided with a step activity monitor (Actigraph GT3X+ (Pensacola, FL, USA)), micro-electro-mechanical system (MEMS) based accelerometer and an ambient light sensor in a standardized orientation to be worn on the paretic and non-paretic ankles for up to seven days with intention to at least obtain measures of daily step activity for a minimum of three days. Participants will be provided with verbal and written instructions to don the device upon waking and doff prior to sleeping unless the participant was bathing or taking part in water-based activities. Daily SS stepping activity for the paretic and non-paretic leg before and after the intervention period will be calculated.

### Harms

Adverse events for the SS will be monitored by the intervention therapist each week during the intervention period. Questions related to levels of pain, fatigue, falls or medical appointments will be asked during the home visits and phone call check-ins. The PI will be notified to evaluate and determine if an event is serious or related to the intervention. While no significant risks have been associated with home-based gait and mobility training, the primary risks associated with the intervention involve fatigue, muscle soreness, frustration attempting challenging tasks, and falls. Additional text and videos related to mobility safety (including instruction in the appropriate use of a safety gait belt) have been incorporated into the CARE-CITE-Gait modules and including examples of collaborative discussions for CP and SS to determine safety during mobility training. Safety issues are discussed during home visits as they relate to goal development and home exercise programs. Study evaluators will monitor SS symptoms, heart rate and blood pressure (and oxygen saturation as appropriate) during gait assessments. A gait belt will be used to reduce fall risk during the evaluation and as appropriate during home visits. Any balance or mobility concerns will be relayed to the PI and study interventionist. Risks associated with CP participation reviewing the intervention modules is minimal. Evaluations will include psychosocial assessments evaluating hrQOL and mood while providing care for the stroke survivor. If the study evaluator notices areas of concern (e.g., potential depressive symptoms) the PI will be notified and will recommend to the CP a referral to their primary health care provider for further assessment. Additional community resources will be provided if needed. This process will be explained in the consent form at the initiation of the study. Adverse events will be documented and categorized based on the following University Internal Review Board protocol: serious (death, life-threatening or related inpatient hospitalization) or non-serious; anticipated or unanticipated; related, potentially related, or non-related to the intervention. Description of the event, date, action taken by participant and study personnel (as appropriate), outcomes and any consequent modification of study intervention or procedures will be included in the event description. A Data Safety and Monitoring Board was not established due to minimal CP and SS participation risks. The study team (PI, Co-I, and statistician) will review all adverse events to determine whether any safety concerns warrant trial termination. Safety considerations arising during study evaluations and interventions will be discussed during regular study staff meetings.

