#### Sample size estimation

For Phase II, given the time required to adapt the intervention, the proposal timeline, and preliminary data from our upper extremity intervention, a sample size of 15 dyads is proposed to evaluate feasibility (2-3 dyads/month). An attrition rate of ~8% is projected based on the literature and our previous work [30]; thus, we will enroll 16 dyads to achieve a final sample of 15. Assuming a two-tailed alpha=0.05, we will have 80% power to detect an effect size=0.78 (Cohen, large), and can calculate 95% confidence intervals within 0.64 standard deviations. These data will provide precision to the estimates of mean changes, variability, and effect sizes for key outcomes. Importantly, these data will inform sample size estimation and identify feasibility lessons to guide our planned next step - a randomized clinical trial evaluating the efficacy of CARE-CITE-Gait.

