Recruitment	Recruitment rates will be the percentage of those participants enrolled and randomized from those screened. Recruitment will be deemed feasible if the target enrollment of 15 dyads (2-3 dyads per month) is reached during the study timeframe.
Retention	Retention of participants will be the percentage of dropouts. An acceptable retention rate will be 85% of enrolled participants for completion of post-evaluation (80% for one-month follow-up).
Intervention Adherence*	CP adherence will be the number of modules reviewed (6 total modules) as indicated by the reflection questions completed at the end of each section. Criteria for CP adherence will be a minimum completion of 5 of the 6 modules. *Study staff are electronically notified of module completion in real-time which allows for reminders to be sent to participants to review modules as needed*. Criteria for CP and SS adherence will be >3.5 hours (for two home visits) and CP completion of week 2 and 3 phone calls.
Safety	Number and type of adverse events (serious vs. non-serious; related or possibly related to CARE-CITE-Gait

* Adherence to the intervention will be evaluated only in the participants completing a baseline and a post-intervention evaluation. SS-stroke survivor; CP-carepartner

**Table 4. T4:** Outcome measures collected at baseline, post-intervention, and 1-month follow-up

Variable	Measure	Description	Reliability/Validity
SS Gait Speed*	10-meter walk test^32^	Time to complete a standardized overground distance; correlated with functional ambulation categories	Excellent test-retest (ICC>0.95),[38] intra- and inter-rater reliability (ICCs>0.87); established construct [39]and criterion[40] validity in stroke
SS Endurance	6-minute walk test^33^	Distance walked in 6-minutes; measure of aerobic capacity and long-distance walking function	SEM, MDC, and MCID published in older adults and stroke; excellent reliability (ICC>0.99); validity established in stroke[39, 41, 42]
SS Dynamic Balance and Functional Mobility*	5-times Sit to stand (5STS)^34^ Timed up and go test (TUG)^35^	Timed tests of functionally relevant lower limb activities (sit to stand, walking, turning)	5STS - Criterion validity with leg muscle strength in stroke; discriminates stroke versus able-bodied;[43, 44] [45] TUG – SEM, MDC, reliability, validity published in stroke[39, 46, 47]

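### The serious-event definition attaches an undefined 'related' to hospitalization, overlapping the separate causality scale; on the likelier reading it can lower the serious-event tally

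*Protocol article*

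**What the plan says.** The Harms section gives one classification sentence with three parts, seriousness, expectedness and causality: "serious (death, life-threatening or related inpatient hospitalization) or non-serious; anticipated or unanticipated; related, potentially related, or non-related to the intervention". The qualifier in the seriousness part stands before hospitalization only; death and life-threatening events carry none. The sentence presents the scheme as the University review board's classification.

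The same section says who decides: "The PI will be notified to evaluate and determine if an event is serious or related to the intervention". It also says that the study team (PI, Co-I and statistician) "will review all adverse events to determine whether any safety concerns warrant trial termination", and that no data safety and monitoring board was set up.

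The Safety row of Table 3 defines the outcome as "Number and type of adverse events (serious vs. non-serious; related or possibly related to CARE-CITE-Gait". Safety is listed in the primary Phase II objective at the end of the Background. Under Sample size estimation, the plan is that "we will enroll 16 dyads to achieve a final sample of 15".

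**The concern.** Seriousness describes the outcome of an event; causality describes its likely origin. The sentence separates the two and then brings causality back into one branch of seriousness. Whether an admission is serious may then depend on a judgement of its cause.

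That matters here for three reasons. The split between serious and non-serious events is one of the two ways Table 3 describes safety. The design has one group, so the PI judges causality without a comparator. Falls are among the primary risks that the Harms section names, so an admission of uncertain cause is foreseeable. At stake is whether the serious-event tally carried forward to the planned randomized trial means what a reader will take it to mean.

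**Working it through.** The protocol article states no adverse event count, rate or safety threshold, so there is no figure to reproduce. The check is of the wording, followed by an illustration of scale.

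**Step 1. What 'related' can refer to.** The word has no object in the seriousness part. There are two candidates:

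- Reading A: related to the intervention. The causality part of the same sentence uses the word this way, with the object stated. So do the sentence on the PI's assessment and the Safety row of Table 3.
- Reading B: related to the adverse event, that is, an admission for that event.

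**Step 2. How each reading classes an admission.**

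| Admission | Causality code | Reading A | Reading B |
|---|---|---|---|
| Fatal or life-threatening | any of the three | serious | serious |
| Neither | related | serious | serious |
| Neither | potentially related | non-serious | serious |
| Neither | non-related | non-serious | serious |

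The readings differ only for admissions that are neither fatal nor life-threatening, and there for two of the three codes.

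**Step 3. Direction.** Every event that is serious under A is also serious under B. Hence the serious count under A is at most the count under B, and any bias from reading A is downward.

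**Step 4. What reaches Table 3.** If the bracket in the Safety row lists two attributes by which all events are described, both differing rows of the table above affect the reported split. If it restricts the tally to related or possibly related events, only the potentially related row does.

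**Step 5. Scale, for illustration.** Input: 16 enrolled dyads, hence 16 stroke survivors (Sample size estimation).

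- One survivor with a reclassified admission: 0/16 = 0% becomes 1/16 = 6.25%, about 6.3%.
- Let p be the chance that a survivor has an admission that is neither fatal nor life-threatening and is not coded related. The documents give no p. Assume 2% to 10%, independent between survivors. The chance of at least one survivor with such an admission is 1 − (1 − p)^16, and the expected number of such survivors is 16p.

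| Assumed p | 1 − (1 − p)^16 | 16p |
|---|---|---|
| 2% | 1 − 0.98^16 = 27.6% | 0.32 |
| 5% | 1 − 0.95^16 = 56.0% | 0.80 |
| 10% | 1 − 0.90^16 = 81.5% | 1.60 |

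On reading A, each such admission would be missing from the serious count. On reading B, none would.

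**The case against.** The strongest reply is that this is loose wording rather than a wrong rule. The sentence gives causality its own scale, and Table 3 names seriousness and relatedness as separate attributes. That layout suggests the authors meant to keep them apart, which favours reading B. The sentence is also a journal article's short account of an institutional classification that is not shown, so the operative form may not contain the qualifier. Finally, Table 3 sets criteria for recruitment, retention and adherence but none for safety, so no feasibility decision turns on the label.

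Much of this stands. The text does not exclude reading B, the source classification cannot be checked, and no criterion changes. Two things remain. First, where the article applies the word to events and states its object, the object is the intervention, so reading A is the more natural one. Second, reading B does not repair the sentence: an admission being classified as an adverse event is already tied to that event, so the word adds almost nothing, and two coders could still file the same admission differently. Nor is this a complaint about detail left to a fuller document, because the article prints the definition.

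**Conclusion.** The point holds as a defect of definition with a possible downward bias in one tally. On reading A, admissions that are neither fatal nor life-threatening and are coded potentially related or non-related are classed non-serious. On reading B, the word is redundant and unclear. One affected survivor would be 1 of 16 (6.3%); the probabilities in the illustration rest on assumed admission rates.

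A reader might infer more than the documents support:

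- That serious events are in fact undercounted. This follows on one reading only, and the article reports no adverse events. Trial Status says only that 90% of participants have been recruited.
- That an admission not coded related can never be serious. A fatal or life-threatening admission is serious whatever its code.
- That the decision on trial termination is weakened. That review covers all adverse events, not only serious ones.
- That events would be lost. Each is documented with its description, date, action taken and outcome, so only the label is at risk.

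No sample size, power or significance-level figure is affected.

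**What to change.** In the Harms section, delete 'related' from the definition of serious, leaving causality to its own scale. Alternatively, keep the word and state that it means an admission for the adverse event, whatever its causality. Check the chosen wording against the review board classification that the section cites, so that article, data forms and institutional rule agree. Apply it to any hospitalizations recorded, and report a cross-table of seriousness by relatedness, so that a reader can see serious events of every causality code.

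The cost is a change of one word or one clause, notice to the review board if the operative protocol carries the same wording, and a check of whatever admissions exist among about 16 survivors. With recruitment at 90%, this can be done before results are reported. The downside is that the reported serious-event count may rise.
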